### Study sample

2.3

All patients diagnosed with COPD are eligible to participate in the study. Additionally, participants must meet the following criteria:

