#### Secondary outcomes

2.8.2

Changes in self-management behaviors: including diet, physical activity, medication adherence, smoking management, alcohol management, sleep management, quality of life, and activities of daily living.

Social Cognition and Psychological Factors: COPD knowledge literacy, self-efficacy, depression, anxiety, stress, and social support.

Control of physiological indicators: cough, breathlessness, blood pressure, height, and weight.

30-days readmission rate: additionally, recruitment rates, dropout rates, and reasons for withdrawal will be collected. To assess the homogeneity of the data, demographic characteristics and outcomes of those who dropped out, as well as those with resistance to the trial, will be compared during the data analysis process.

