### Variables measurement

2.9

Sociodemographic variables will be obtained at baseline. Physical examinations and questionnaires will be completed at baseline, discharge, and end of intervention, and at 3, 6, and 9 months post-intervention (Table 1).

**TABLE 1 T1:** The schedule of enrollment, interventions, and assessments.

Study period	Recruitment	Intervention		Follow-up		
Timepoint	0	Discharge	3 months	3 months	6 months	9 months
Eligibility screen	√					
Informed consent	√					
Allocation	√					
Sociodemographic variables	√					
CAT	√	√	√	√	√	√
mMRC	√	√	√	√	√	√
CET	√	√	√	√	√	√
PHQ4	√	√	√	√	√	√
PSSS-SF	√	√	√	√	√	√
NGSES-SF	√	√	√	√	√	√
EQ-5D-5L	√		√	√	√	√
Smoking	√		√	√	√	√
Alcohol consumption	√		√	√	√	√
B-PSQI	√		√	√	√	√
FCS-SF	√					
eHEALS	√					

B-PSQI, The new Brief Version of the Pittsburgh Sleep Quality Index-Short Form; CAT, COPD Assessment Test; CET, Cough Evaluation Test; eHEALS, The eHealth Literacy Scale; EQ-5D-5L, EuroQol-5 Dimensions 5 Levels; FCS-SF, The Family Communication Scale-Short Form; IPAQ-SF, The International Physical Activity Questionnaire Short Form; mMRC, Modified Medical Research Council; PHQ-4, the abbreviated Patient Health Questionnaire-4; PSSS-SF, The Perceived Social Support Scale; NGSES-SF, The New General Self-Efficacy Scale-Short Form; SREBQ, The Self-Regulation of Eating Behavior Questionnaire.

After discharge, we will maintain contact with participants via WeChat, telephone, or text messages to ensure they stay well-informed and remain actively engaged. During these interactions, participants will receive timely updates on study progress, solutions to any emerging issues, and timely reminders for upcoming follow-up assessments.

Standardized data entry for this study will be conducted using an electronic data capture (EDC) system. First, double data entry will be performed by two independent operators to ensure accuracy, followed by logical validation checks on all raw data. Sensitive information will be encrypted using the Unicode encoding scheme. Data will be stored on password-protected servers with role-based access control (where only authorized researchers can access de-identified data), and a real-time backup system will be deployed to off-site cloud storage to ensure data integrity and disaster recovery capabilities.

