Smoking behavior will be assessed using a self-designed questionnaire consisting of four multiple-choice questions, aimed at categorizing respondents based on their smoking habits (26). These questions are intended to determine whether the individual currently smokes, how many years they have been smoke-free, their daily smoking consumption, and their age when they started smoking. The first question asks: “Do you currently have a smoking habit?” The response options are: (1) Yes, I smoke regular cigarettes; (2) Yes, I smoke e-cigarettes; (3) I smoke both; (4) I used to smoke (currently quit); (5) I have never smoked. Based on the responses, participants will be classified into two groups: smokers (current smokers) and non-smokers (never smoked or quit).

Drinking behavior will also be evaluated using a self-designed questionnaire, which includes seven multiple-choice questions designed to gain detailed insights into the respondents’ drinking habits. These questions cover aspects such as whether the respondent drinks alcohol, their age at first use, age at cessation, types of alcohol consumed, daily alcohol intake, their average daily consumption before quitting, and any anxiety experienced during the quitting process. The respondents will be asked: “Do you currently drink alcohol, or have you drunk in the past?” The response options are: (1) Never drank; (2) Always drink; (3) Drank in the past but do not drink now; (4) Did not drink before, but now drink.

The Pittsburgh Sleep Quality Index Short Form (PSQI-SF) is a condensed version of the Pittsburgh Sleep Quality Index, specifically designed to assess an individual’s sleep quality (27). This scale consists of six items covering five key dimensions: sleep efficiency (items 1 and 2), sleep onset latency (item 3), sleep duration (item 4), sleep disturbances (item 5), and overall sleep quality (item 6). The sleep onset and wake-up time data are used to calculate sleep efficiency. The total score ranges from 0 to 15, with higher scores indicating poorer sleep quality, reflecting greater sleep difficulties.

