### Statistical analysis

2.11

We will collect quantitative data using a structured questionnaire and then input it into Microsoft Excel for analysis. All major analyses will follow intention to treat (ITT) and will undergo protocol compliant (PP) analysis for sensitivity testing. Descriptive statistics will be used to summarize feasibility variables such as starting information, number of participants, and system usage. For continuous data, the mean and standard deviation of normally distributed data, as well as the median and 25th to 75th percentile of non-parametric data, will be provided. To compare the untreated group and the group measured once, independent sample *t*-tests and their non-parametric analogues will be used. The categorical data will be expressed in frequency and percentage, and analyzed using chi square test. The normality of the data will be tested using the Kolmogorov Smirnov test. Under the assumption of random missing data, established multiple imputation methods will be used in appropriate circumstances to handle the missing data. We will examine and compare the missing and wear patterns between each group to identify potential differences in dropout rates, and conduct sensitivity analysis to compare estimated and complete case outcomes. For the main experiments, the focus will be on using a linear mixed effects model to evaluate the main outcome indicators. For secondary outcomes such as self-management and psychosocial/cognitive outcomes, analysis will use similar mixed effects models or simpler comparison methods, depending on the nature and timing of data collection. In addition, exploratory age stratification analysis can be conducted to examine the potential heterogeneity of intervention effects across different age groups in a descriptive manner. Given the pilot nature of the study, the results should be interpreted with caution. The measurement criteria used by the system, such as the number of questions, will be summarized in a descriptive manner and can be included as covariates in exploratory analysis to better understand compliance patterns; these analyses will be seen as hypothesis generation rather than validation. All statistical tests are two-sided, with a significance level of 0.05. Data analysis will be conducted using IBM SPSS Statistics (version 24.0; SPSS Inc., Chicago, Illinois, USA and Stata (version 14.0); StataCorp, College Station, TX, The United States) conducted.

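### The two-level smoking variable merges never-smokers with quitters; if compared across all participants without baseline status, it shrinks a quit effect by the baseline smoker share

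*Protocol article*

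**What the plan says.** - **Coding.** The first smoking question in section 2.10 (Questionnaires) has five responses. Three are forms of current smoking, and the last two are kept apart: "4) I used to smoke (currently quit); (5) I have never smoked". The other items cover "how many years they have been smoke-free, their daily smoking consumption, and their age when they started smoking". The section then reduces the responses to two levels: "participants will be classified into two groups: smokers (current smokers) and non-smokers (never smoked or quit".
- **Role.** Section 2.8.2 (Secondary outcomes) lists "Changes in self-management behaviors: including diet, physical activity, medication adherence, smoking management, alcohol management" and further behaviors.
- **Timing.** Section 2.9 says in general that "Physical examinations and questionnaires will be completed at baseline, discharge, and end of intervention, and at 3, 6, and 9 months post-intervention". For smoking, Table 1 marks baseline, end of intervention, and 3, 6 and 9 months afterwards, and leaves discharge blank.
- **Who enters.** Section 2.3 opens with "All patients diagnosed with COPD are eligible to participate in the study", and no inclusion or exclusion criterion refers to smoking.
- **Analysis.** Section 2.11 sets intention to treat for the major analyses and states: "The categorical data will be expressed in frequency and percentage, and analyzed using chi square test". For secondary outcomes, self-management among them, it allows mixed models or simpler comparisons according to the nature and timing of the data. Age is the only stratification named.

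**The concern.** The outcome is a change in behavior, but the two-level variable at a follow-up visit does not show change. A patient who quit last month and one who never smoked receive the same value. Never-smokers cannot quit, so they carry no information on cessation. Ex-smokers carry information on relapse only.

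Smoking status does not limit eligibility, so all three kinds of patient can enter. Chi-square on follow-up status, if applied to everyone, would compare current smoking prevalence between arms. That prevalence depends largely on who smoked at entry.

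Two things are at stake: the size of the reported smoking effect, and its precision. Section 2.4 makes the pilot a source of effect sizes and variances for the main trial, so an attenuated estimate could be carried forward if cessation were planned for there. The article does not say that the main trial would be sized on smoking.

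**Working it through.** **Inputs from the article.** Recruitment is 30 per group, with about 25 per group expected after attrition (section 2.4). The stated target reproduces: 25/(1 − 0.15) = 29.4, so 30 per group at mid-range attrition; also 50 × 1.20 = 60. The article gives no sample size, power or rate for smoking.

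**Assumptions.** Baseline smoker share s = 0.3 to 0.5. Quit rates among baseline smokers are 30% vs 10%, or 40% vs 20% (intervention vs control). Baseline non-smokers stay non-smokers.

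**Step 1: size of the effect.** Follow-up smoking prevalence in an arm is s × (1 − q), where q is its quit rate. The between-arm difference in the whole sample is therefore s × (q_int − q_ctl):
- s = 0.3: 0.3 × 20 = 6 points
- s = 0.4: 0.4 × 20 = 8 points
- s = 0.5: 0.5 × 20 = 10 points

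**Step 2: signal relative to noise, 30 per arm.** Whole sample: SE = √[(p1(1 − p1) + p2(1 − p2))/30]. Baseline smokers: SE = √[(q1(1 − q1) + q2(1 − q2))/(30s)].

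Example, s = 0.4, quit 30% vs 10%:
- Whole sample: p = 0.36 vs 0.28, SE = √(0.432/30) = 0.120, z = 0.08/0.120 = 0.67.
- Baseline smokers (12 per arm): SE = √(0.30/12) = 0.158, z = 0.20/0.158 = 1.26.

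| s | Quit rates | z, whole sample | z, baseline smokers |
|---|---|---|---|
| 0.3 | 30% vs 10% | 0.55 | 1.10 |
| 0.3 | 40% vs 20% | 0.57 | 0.95 |
| 0.5 | 30% vs 10% | 0.79 | 1.41 |
| 0.5 | 40% vs 20% | 0.82 | 1.22 |

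The ratio runs from 1.5 to 2.0.

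**Step 3: where the noise comes from.** In the example, the variance numerator 0.432 splits into two parts. Chance variation in who smoked at baseline gives 0.24 × (0.9² + 0.7²) = 0.312. Variation in quitting gives 0.4 × (0.09 + 0.21) = 0.120. So 0.312/0.432 = 72% of the variance is baseline smoking status. Put differently, the chance SD of the between-arm difference in baseline smoking is √(2 × 0.24/30) = 12.6 points, against a diluted effect of 8 points.

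**Step 4: power at two-sided 0.05, quit 30% vs 10%.** With 25 per arm, whole sample vs baseline smokers: 7% vs 15% at s = 0.3, and 11% vs 23% at s = 0.5. Simulation (20,000 runs) gives 8% vs 12% and 13% vs 23%. With 200 per arm, simulated power is 29% vs 80% at s = 0.3 and 53% vs 95% at s = 0.5.

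**Step 5: planning consequence.** For 80% power, a whole-sample comparison needs 795 per arm at s = 0.3 and 376 at s = 0.5. An analysis of baseline smokers needs 62 smokers per arm, that is 62/0.3 = 207 or 62/0.5 = 124 enrolled per arm.

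**The case against.** The strongest reply is that the article never says smoking will be compared across the whole sample. The chi-square sentence stands among general rules for summarizing data. The sentence on secondary outcomes covers self-management behaviors and leaves the method open. The outcome is worded as change, and smoking is measured at baseline, so a longitudinal analysis could use baseline status. An analysis plan that is not shown may fix the denominator. All of this stands, and it is why the point is conditional. It does not remove the stated coding, which merges the two kinds of non-smoker at every visit, and nothing in section 2.11 offsets it for smoking.

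Other parts of the reply also stand:
- The article names smoking management, not cessation. Smoker versus non-smoker is a legitimate summary and also picks up relapse.
- No data are lost, because the original responses are collected.
- Power is poor either way at pilot size. Section 2.4 says hypothesis testing is not the pilot's primary objective.
- All prevalences and quit rates used here are assumed.

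A reader might go further and infer that a baseline imbalance would bias the result. Under randomization it does not: it is sampling variation already contained in the standard error, and it costs precision. A reader might also infer that all non-smokers are unable to change. That is true of never-smokers with regard to quitting, but ex-smokers can relapse.

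**Conclusion.** The point holds in conditional form. The merge of never-smokers and quitters is stated, and no baseline-smoker denominator or baseline adjustment accompanies it. If that variable is compared across all participants without baseline status, the risk difference for quitting is multiplied by the baseline smoker share. That factor is exact when baseline non-smokers stay non-smokers.

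With an assumed share of 30% to 50%, 20 points become 6 to 10. With 30 per arm, expected z is 0.55 to 0.82, against 0.95 to 1.41 among baseline smokers. Neither reaches 1.96, so the better definition does not turn the pilot into a test of cessation. Its value is an estimate that describes quitting and can be used for planning. The documents do not support saying that the plan commits to the diluted comparison, or that it would produce a false effect. The weight is minor: one component of a secondary outcome in a pilot.

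**What to change.** In sections 2.10 and 2.11:

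1. Keep the five response levels in the analysis data.
2. Report cessation (response 4) at end of intervention and at 3, 6 and 9 months among participants who were current smokers at baseline (responses 1 to 3), as a between-arm difference with a confidence interval.
3. Report relapse (responses 1 to 3 at follow-up) among baseline ex-smokers separately.
4. If the two-level variable is kept for the whole sample, adjust for baseline smoking status. This removes the noise shown in step 3 of the working. A risk difference averaged over everyone would still be s times the quit difference and should be described as such.

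The cost is wording only, because every item is already collected at the visits needed. The drawback is a small denominator: 9 to 15 baseline smokers per arm out of 30 under the assumed shares, fewer after attrition. The interval will be wide, and the result should be labelled descriptive.

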### Statistical analysis

2.11

We will collect quantitative data using a structured questionnaire and then input it into Microsoft Excel for analysis. All major analyses will follow intention to treat (ITT) and will undergo protocol compliant (PP) analysis for sensitivity testing. Descriptive statistics will be used to summarize feasibility variables such as starting information, number of participants, and system usage. For continuous data, the mean and standard deviation of normally distributed data, as well as the median and 25th to 75th percentile of non-parametric data, will be provided. To compare the untreated group and the group measured once, independent sample *t*-tests and their non-parametric analogues will be used. The categorical data will be expressed in frequency and percentage, and analyzed using chi square test. The normality of the data will be tested using the Kolmogorov Smirnov test. Under the assumption of random missing data, established multiple imputation methods will be used in appropriate circumstances to handle the missing data. We will examine and compare the missing and wear patterns between each group to identify potential differences in dropout rates, and conduct sensitivity analysis to compare estimated and complete case outcomes. For the main experiments, the focus will be on using a linear mixed effects model to evaluate the main outcome indicators. For secondary outcomes such as self-management and psychosocial/cognitive outcomes, analysis will use similar mixed effects models or simpler comparison methods, depending on the nature and timing of data collection. In addition, exploratory age stratification analysis can be conducted to examine the potential heterogeneity of intervention effects across different age groups in a descriptive manner. Given the pilot nature of the study, the results should be interpreted with caution. The measurement criteria used by the system, such as the number of questions, will be summarized in a descriptive manner and can be included as covariates in exploratory analysis to better understand compliance patterns; these analyses will be seen as hypothesis generation rather than validation. All statistical tests are two-sided, with a significance level of 0.05. Data analysis will be conducted using IBM SPSS Statistics (version 24.0; SPSS Inc., Chicago, Illinois, USA and Stata (version 14.0); StataCorp, College Station, TX, The United States) conducted.

After the intervention, we will conduct structured interviews with participants to assess the attractiveness, acceptability, usability, and overall satisfaction with the intervention program. These interviews will help explore key factors influencing engagement and behavior change in greater depth. Approximately 30-min telephone or face-to-face in-depth interviews will be scheduled. Demographic variables such as gender, age, location, education level, and severity of COPD will be considered when selecting interview participants. The interview topics will focus on personal experiences, suggestions for improving the AI-HEALS system, motivations for maintaining self-management behaviors, and challenges encountered. To ensure the collection of rich and diverse data, we will continue recruiting participants until data saturation is reached. All interviews will be audio-recorded and transcribed verbatim, ensuring anonymity, and analyzed using a theoretical framework within NVivo 12 (Version 12, QRS International, Doncaster, Australia). Furthermore, qualitative data will be integrated with quantitative data to provide a more comprehensive interpretation of the outcomes at each phase of the trial. This approach will offer a more holistic perspective on the intervention’s effects and its long-term impact on participants.

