### Randomization and blinding

2.2

In this research, a computer-generated random number sequence will be applied in randomization. Patients will be assigned to intervention and standard care groups in a 1:1 ratio. Randomization will be carried out prior to their hospital admission. Through this process, every patient will be assigned to their corresponding study group based on a predetermined sequence to ensure randomness and equity of allocation. Upon entering their ward, each patient will receive a unique code that is equivalent to the random number sequence for facilitation of smooth and uninterrupted recruitment. Once randomization is completed, patients will be transferred to their respective ward depending on their assigned groups. Specifically, intervention patients will be admitted to Ward A, with patients in the control arm going to Ward B to avoid possible cross-contamination between different treatments.

In order to maintain confidentiality of sequence allocation, an independent team member not involved in participant registration or in intervening in any way in the allocation process will perform randomization. This step aims to avoid revealing the randomization sequence during the study. The allocation outcome will then be communicated by the independent team member to the intervention team so that neither the participant registration team nor intervention team knows beforehand against which group a participant is registered.

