### Sample size

2.4

This RCT will be conducted in two sequential phases. The first phase serves as a pilot study aiming to obtain preliminary estimates of the intervention’s effect size, variability, and feasibility parameters. These pilot data will provide empirical inputs for calculating the appropriate sample size required for the subsequent full-scale RCT.

In this pilot phase, the primary objective is not hypothesis testing but to estimate outcome variance and effect size with sufficient precision to inform future sample size determination. Following commonly recommended practices for pilot RCTs (17), approximately 25 participants per group (about 50 in total) will be recruited. Considering an anticipated 10%–20% attrition rate, the total recruitment target is set at 60 participants (30 per group).

The effect size derived from this pilot phase will then be used to conduct a formal power analysis to determine the optimal sample size for the main RCT, ensuring adequate statistical power to test the study hypotheses.

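### Section 2.11 lets secondary outcomes that have a baseline be compared by unadjusted tests, and does not confine the post-randomisation usage covariate to the intervention arm

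*Protocol article*

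**What the plan says.** Section 2.11 commits the primary outcome, CAT, to a linear mixed effects model. For the secondary self-management and psychosocial or cognitive outcomes it leaves the method open: "analysis will use similar mixed effects models or simpler comparison methods, depending on the nature and timing of data collection". The simple methods described in the same section are independent-sample t-tests, their non-parametric analogues and the chi-square test. It adds that "The normality of the data will be tested using the Kolmogorov Smirnov test", and that "All statistical tests are two-sided, with a significance level of 0.05".

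Table 1 (section 2.9) schedules PHQ-4, PSSS-SF, NGSES-SF, EQ-5D-5L and B-PSQI at baseline and at several later visits.

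On system usage, section 2.11 says that the measures, "such as the number of questions, will be summarized in a descriptive manner and can be included as covariates in exploratory analysis". It ties this to understanding compliance and labels it hypothesis-generating. Section 2.7.1 states that controls have no access to the system.

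Section 2.4 describes this phase as a pilot in which "the primary objective is not hypothesis testing but to estimate outcome variance and effect size with sufficient precision" is the aim. It plans that "approximately 25 participants per group (about 50 in total) will be recruited" and raises the target to 60 (30 per arm) for attrition of 10% to 20%.

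**The concern.** There are two separate issues.

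**Baseline.** A scale measured before and after the intervention carries information in its baseline value. A two-sample test on follow-up scores ignores it. With about 25 patients per arm that information is worth having, and section 2.4 makes precise estimation the purpose of the phase. The plan permits the less precise analysis for outcomes where the better one needs no extra data.

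**Usage.** The number of questions asked arises after randomisation, can be affected by health and motivation, and is zero for every control. If it is put in a model that also contains the arm, the arm coefficient no longer compares the randomised groups. It becomes an extrapolation to intervention patients with no use. Calling such an analysis exploratory does not make that coefficient interpretable.

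**Working it through.** **1. The plan's own figure.** 50 evaluable patients inflated by N/(1 - d): 50/0.90 = 55.6, so 56; 50/0.80 = 62.5, so 63. The stated 60 lies in this range and corresponds to d = 16.7%. With 60 recruited, 60 × 0.80 = 48 to 60 × 0.90 = 54 remain, so 25 per arm is a fair working size. The plan states no power, SD or correlation, so none can be reproduced.

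**2. Cost of leaving out the baseline.** For a follow-up score with equal arms, variance with baseline adjustment divided by variance of the follow-up-only comparison = 1 - r², where r is the correlation between baseline and follow-up (ignoring the one degree of freedom spent). The detectable difference at 80% power, two-sided 0.05, 25 per arm, is (1.960 + 0.842) × √(2/25) = 0.79 SD unadjusted. With adjustment it is multiplied by √(1 - r²). The document gives no r, so a range is shown.

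| r (assumed) | Variance cut | 25 per arm act like 25/(1 - r²) | Detectable difference, SD | Power for an assumed 0.5 SD |
|---|---|---|---|---|
| unadjusted | – | 25 | 0.79 | 42% |
| 0.3 | 9% | 27 | 0.76 | 46% |
| 0.5 | 25% | 33 | 0.69 | 53% |
| 0.6 | 36% | 39 | 0.63 | 60% |
| 0.7 | 49% | 49 | 0.57 | 70% |

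Power is shown only as a scale for precision, since the pilot is not designed to test hypotheses.

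**3. Usage in a between-arm model.** Let usage have mean m and SD s in the intervention arm and be 0 in controls. Then:

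- Arm coefficient = total arm effect - (slope of outcome on usage within the intervention arm) × m.
- Squared correlation of arm and usage = m²/(m² + 2s²). With m = 2s (assumed) this is 4/6, so the standard error grows by about √(1/(1 - 4/6)) = √3 = 1.73.

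Simulation with assumed values (25 per arm, r = 0.5, usage mean 20 and SD 10, true arm effect 0.50 SD, 3,000 runs per case):

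| Assumed mechanism | Arm coefficient without usage | With usage | SE without | SE with |
|---|---|---|---|---|
| Effect runs wholly through usage | 0.50 | 0.00 | 0.25 | 0.45 |
| Usage has no effect but shares a cause with the outcome | 0.50 | 0.01 | 0.25 | 0.44 |
| Usage unrelated to the outcome | 0.50 | 0.51 | 0.25 | 0.45 |

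The first row agrees with the formula: slope 0.025 × mean 20 = 0.50, and 0.50 - 0.50 = 0. The formula also gives a case with no true effect: a within-arm correlation of -0.3 and mean use of 2 SD give 0 - (-0.3 × 2) = +0.6 SD.

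**4. The normality test.** In 3,000 simulated pairs of 25 per arm, the Lilliefors version of the Kolmogorov-Smirnov test rejected in at least one arm in 9% of runs for normal data, 45% for a 3 to 15 integer score and 88% for a skewed 0 to 12 score. Choosing between t-test and rank test on that result kept type I error at 0.051, 0.053 and 0.047.

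**The case against.** The best defence on baseline is that the choice depends on the timing of data collection, and that the sentence on t-tests mentions a group measured once. Simple tests may therefore be meant for outcomes such as 30-day readmission, which has no baseline, while repeated scales take the mixed model. This may be the intention. But the t-test sentence is garbled, and the sentence that offers the choice has as its subject the outcomes whose scales Table 1 repeats from baseline. The reading is possible, not secured. A reader should equally not infer that every secondary scale will get a t-test; the document does not say that. Per-outcome model detail may also sit in an analysis plan not shown. The point is therefore what the text permits, not what it omits.

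On usage, the text is optional, exploratory and aimed at compliance, which points towards an analysis within the intervention arm. It names no between-arm model, so a reader who infers that the trial's arm effects will be biased goes further than the document. One of the three simulated cases shows no bias, and the size of the others depends on assumed values. What stands is that nothing confines the covariate to the intervention arm.

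A reader might also infer that the Kolmogorov-Smirnov test is a gate that hardly ever rejects at this size, or that it damages the error rate. Neither is supported. The document does not state the test as a decision rule or say which version is used. The corrected version rejects often on short integer scores, and type I error stays near 5%. At most it makes the choice of summary and test depend on the data; it causes neither the loss of precision nor the possible bias.

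**Conclusion.** The point holds in two limited parts.

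- **Baseline:** section 2.11 permits an unadjusted comparison of secondary outcomes whose baseline is collected. Where that option is taken, 9% to 49% of the variance could have been removed for r between 0.3 and 0.7. That range is an assumption.
- **Usage:** the covariate is post-randomisation and structurally zero in controls, and it is not limited to the intervention arm. If it entered a between-arm model, the standard error would rise by a factor of about 1.7 to 1.8 when mean use is 2 SD, and the arm coefficient could be seriously wrong unless usage were unrelated to the outcome. This is conditional on a model that the document does not name.

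The planned mixed model for CAT is not affected by the baseline part. Importance is low to moderate: these are secondary and exploratory analyses of a pilot. The baseline part still bears on the pilot's own aim of precise estimation.

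**What to change.** Change the wording of section 2.11 in three places:

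1. For every continuous secondary outcome with a baseline, use the mixed model, or ANCOVA if there is one post-baseline time, with the baseline value included whatever the normality test shows. State how baseline enters, as a covariate or through a common baseline mean. A plain contrast of changes has variance 2(1 - r) relative to the follow-up-only test, which is 1.4 at r = 0.3, so it does not secure the gain.
2. Keep t-tests, rank tests and chi-square tests for outcomes without a baseline, such as 30-day readmission, and say so.
3. Analyse usage within the intervention arm only, adjusted for baseline values, and keep it out of any model that estimates the arm effect. The association can still be confounded and should be reported as such. If eHEALS is one of the adjusters, reconcile Table 1, which schedules it at baseline, with the Discussion, which says digital health literacy is not formally measured.

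The cost is a few sentences and a little programming. Table 1 already schedules the data needed.
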